## Abstract

**Background:**

Health TAPESTRY (Health Teams Advancing Patient Experience: STRengthening qualitY) aims to help people stay healthier for longer where they live by providing person-focused care through the integration of four key program components: (1) trained volunteers who visit clients in their homes, (2) an interprofessional primary health care team, (3) use of technology to collect and share information, and (4) improved connections to community health and social services. The initial randomized controlled trial of Health TAPESTRY found promising results in terms of health care use and patient outcomes, indicating a shift from reactive to preventive care. The trial was based on one clinical academic center, thus limiting generalizability. The study objectives are (1) to test reproducibility of the established effectiveness of Health TAPESTRY on physical activity and hospitalizations, (2) to test the feasibility of, and understand the contributing factors to, the implementation of Health TAPESTRY in six diverse communities across Ontario, Canada, and (3) to determine the value for money of implementing Health TAPESTRY.

**Methods:**

This planned study is a pragmatic parallel randomized controlled trial with a delayed intervention for control participants at 6 months. This trial will simultaneously assess effectiveness and implementation in a real-world setting (type II hybrid) in six diverse communities across Ontario. Participants 70 years of age and older will be randomized into the Health TAPESTRY intervention or the control group (usual care). Intervention clients will receive an individualized plan of care from an interprofessional care team. The plan will be based on a client’s goals and current health risks identified through volunteer visits. The study’s outcomes are mapped onto the RE-AIM framework, with levels of physical activity and number of hospitalizations as the co-primary outcomes. The main analysis will be a comparison at 6 months.

**Discussion:**

It is important to evaluate the effectiveness and implementation of Health TAPESTRY in multiple communities prior to scaling or widespread adoption.

**Trial registration:**

ClinicalTrials.gov NCT03397836. Registered on 12 January 2018

## Background

With improved living circumstances and health care, the world’s population of older adults is increasing and expected to double by 2050 [1]. Older adults are consistently high users of the health care system and often have complex health needs [2]. As a result, health care systems and associated services are experiencing increasing pressure to meet patient needs in an effective and efficient way. Barriers to delivery of healthcare include a lack of continuity of care and coordinated transitions between health and social care domains, barriers to accessing community services, and poor coordination in addressing social determinants of health [2–4]. Primary care is the central focal point of the health care system for most patients. Primary care providers practice person-focused care (not disease-oriented care) over time for all conditions except very uncommon ones and coordinate and integrate their patients’ care regardless of where care takes place. Primary health care is central to a health care system that can function well to address diverse population needs and improve patient outcomes and is associated with increased population longevity and reduced health care distribution inequities [5–9]. Regardless of what aspect of primary health care is investigated (e.g., access, utilization, enrollment, or availability), the effects of investing in primary care are consistent [10]. Health care systems with strong primary care systems are also associated with more efficient use of services including: lower hospitalization rates, lower health care system costs, and sustainable system development [1]. Research has identified that the key elements that support these positive effects are person-focused care [11, 12], relational continuity [13–15], comprehensiveness [16, 17], first contact care [16], and care coordination [10, 18–20].

The Health TAPESTRY (Health Teams Advancing Patient Experience: STRengthening qualitY) program is a complex person-focused intervention that is anchored in primary care. Health TAPESTRY was designed with some of the current health system barriers in mind and to align with best practices from primary health care research [21, 22] and the Starfield’s principles of primary care delivery [5, 7]. Health TAPESTRY works to help people stay healthier for longer in the places where they live—the basis of engaging patients in a meaningful way is through a conversation about health goals and what matters most to patients in their lives. In an initial randomized controlled trial (RCT) that assessed effectiveness and cost-effectiveness, we found null results for the pre-specified primary outcome of goal attainment, but statistically significant improvements in pre-specified secondary outcomes related to health and health services use [23]. Specifically, we found that more minutes of walking per week and less time spent sitting per week were reported in the Health TAPESTRY group compared to the control group [24, 25]. We also found statistically significant differences in health service use with reduced hospitalizations and increased primary health care visits (including both family physicians and other health care providers) [25], suggesting that Health TAPESTRY may be shifting care from a reactive to a proactive approach.

The Health TAPESTRY program incorporates four parts:
Trained volunteers who meet with clients (i.e., patients enrolled in Health TAPESTRY) in their homes to discuss clients’ health and life goals and unidentified health and health-related social needsThe use of technology for collecting and sharing information with the primary care teamAn interprofessional primary health care team (who meets regularly as a “TAP-Huddle”) to create individualized plans of care based on the data gathered, which is integrated with the patient’s longitudinal primary careCommunity engagement and connections to assist clients to meet their goals and address health risks and needs.

A limitation of the initial RCT was it was only conducted in one established, well-supported academic interprofessional team environment [24]. Since primary health care is diverse in regard to team composition, work flow, and funding models, we wish to test the reproducibility of the results found in the initial trial of Health TAPESTRY set among a broader range of primary care clinics and communities.

### Grounding frameworks

We used the RE-AIM framework (Reach, Effectiveness or Efficacy, Adoption, Implementation and Maintenance (RE-AIM.org) to develop the objectives, research questions, and outcome measures for this implementation study and Normalization Process Theory (NPT) will help us understand the processes of implementation [26, 27]. RE-AIM is a well-recognized framework that has been widely used for evaluating the implementation of health programs [28–30]. The RE-AIM framework can be used in the planning, development, implementation, and evaluation phases of programs. We will use NPT to complement the RE-AIM framework and facilitate an understanding of the implementation process of the Health TAPESTRY approach into routine practice in the different communities [26, 27]. NPT has been applied in primary care settings to study implementation [31].

### Objectives and hypotheses

There are three objectives in this study, which are:
To test reproducibility of the effectiveness of Health TAPESTRY on health service utilization and physical activity compared to usual care that we found in our initial study [24, 25]To test the feasibility of, and understand the contributing factors to, implementation of the Health TAPESTRY program in six diverse communities across Ontario, CanadaTo determine the value for money of implementing Health TAPESTRY

We hypothesize that results will be reproduced from the first trial evaluation such that Health TAPESTRY will result in a reduction in hospitalizations and an increase in physical activity levels, compared to usual care at 6 months, and will be cost-effective compared to usual care.

## Methods/design

### Trial design

This study is a pragmatic parallel randomized controlled trial with a delayed intervention for control participants at 6 months. We will simultaneously assess effectiveness and implementation strategy in a real-world setting (type II hybrid) [32]. The main group comparisons will be at 6 months. We report this study protocol in accordance with the SPIRIT guidelines (see Additional file 1 for the checklist; see Fig. 1 for the SPIRIT Figure) [33] and TIDier checklist (see Additional file 2) [34]. We will use mixed-methods data collection, mapping onto the adoption, implementation, and maintenance domains in RE-AIM.

**Fig. 1 Fig1:**
[figure not shown]
Study timeline and date collection time points

### Study setting

To be an implementation site, a primary care practice must meet a list of inclusion and exclusion criteria (Table 1). Included in the criteria is having partnership or access to an organization responsible for oversight of volunteers to implement the home visits and data collection in Health TAPESTRY.

**Table 1 Tab1:** Health TAPESTRY implementation site inclusion and exclusion criteria

Primary care practice inclusion criteria	Primary care practice exclusion criteria
A primary care practice with a clearly identified practice champion for Health TAPESTRY model	No functional connections to an interdisciplinary primary care team to support individual patient assessments
Interprofessional primary care team available to provide core implementation components	Focused assessment on a single condition or disease
Team-based use of an electronic medical record system for documentation or willingness to engage in team-based use	
Able and willing to use the Health TAPESTRY web-based application (TAP-App)	
Partnership or access to a local organization with volunteer infrastructure with the capacity to recruit, train, sustain, and coordinate volunteers, and ensure volunteers have access to the digital health tools needed to fulfill role	

The study will be conducted within Family Health Teams (FHTs) in six communities across Ontario, Canada. A FHT is a type of primary care delivery model within Ontario that formally connects physicians and other health care professionals (e.g., dietitians, social workers, pharmacists) to improve the quality and effectiveness of primary health care services [35]. FHT team members are often co-located, but not always.

### Participant inclusion and exclusion criteria

Participants must be 70 years of age or older and rostered to a participating primary care physician. Participants will be excluded if they: live in a long-term care facility, are likely to be unavailable for follow-up for the 6-month study period, participated in the first implementation of Health TAPESTRY, or have other conditions or circumstances that would prevent them from engaging with the volunteers or completing the surveys with volunteers (e.g., severe dementia, inability to comprehend English even with caregiver translation). The inclusion and exclusion criteria for participants replicate those of the initial trial of Health TAPESTRY [24, 25].

### Recruitment

The main recruitment strategy is an EMR query run to identify all patients 70 years of age or older and rostered to physicians participating in Health TAPESTRY. Implementation sites (i.e., a participating primary care practice) will develop a recruitment strategy to identify eligible patients that fits the local context. Eligible patients will be mailed an information letter and consent form on behalf of participating physicians at each FHT inviting them to participate. Patients that return a signed consent form (a copy of the consent form is available from the corresponding author by request) will be contacted by a volunteer coordinator to confirm eligibility and review all information within the consent. Secondary recruitment strategies may include providing information in waiting rooms and printed materials for health care providers to hand out.

### Randomization and blinding

After informed consent is obtained, participants will be randomized by a volunteer coordinator into the intervention or control group with a ratio of 1:1 using blocked randomization with variable block sizes of 2, 4, and 6 through REDCap (Version 9.3.1, Vanderbilt University) [36]. Couples who are eligible and both decide to participate in the program will be allocated to the same group by randomizing one person and allocating the second person to the same group. For the main analysis, one person’s data will be randomly selected for inclusion. The health care providers will not be blinded; however, they will only know a participant is receiving the intervention once a Health TAPESTRY report is received. The people (volunteers, researchers) involved in research outcome data collection will not be blinded.

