### Sample size

We estimated the sample sizes for both co-primary outcomes physical activity and number of hospitalizations for different effect sizes, based on the initial trial [24, 25], using Bonferroni adjustment [55], with *α* = 0.025 and power = 0.80, using software PASS v19.0.4 [56]. We selected the total sample sizes 488 for physical activity (corresponding to mean difference = 403 and SD = 1441) and 426 for number of hospitalizations (corresponding to mean difference = − 0.14 and SD = 0.47). Using the larger sample size estimate for physical activity and accounting for 20% lost to follow-up, we will require a sample size of 586 participants.

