### Data analysis

The results will be reported according to the CONSORT extension for pragmatic randomized trials [57] and non-pharmacological interventions [58]. The mean (standard deviation) or median (first quartile, third quartile) for continuous variables, depending on the distribution, and count (percent) for categorical variables will be calculated. The description of the data analysis approach below is separated based on the RE-AIM framework for effectiveness and implementation. Note that for reach, adoption, and maintenance, the analysis approach is found in Table 3.

Effectiveness: the effectiveness of Health TAPESTRY will be assessed at 6 months. We will adopt intention-to-treat (ITT) as the primary analysis approach. Multiple imputation approach using chained equations will be used to impute the missing data [59]. We will consider the fraction of missing information and determine the number of imputations needed using the two-stage approach suggested by Hippel [60]. The pooled effect estimates along with 95% confidence intervals will be reported. The co-primary outcome of a number of hospital admission will be analyzed using the Poisson regression or negative binomial regression depending on the distribution. The incidence rate ratio along with 95% confidence interval will be reported. And the co-primary outcome physical activity will be analyzed using the multiple linear regression. The mean difference between intervention and control group along with 95% confidence intervals will be reported. The continuous outcomes (sitting, patient enablement, quality of life, treatment and disease burden scores) and the count secondary outcomes (number of falls, number of primary care visits, number of emergency room or urgent care visits, number of medications) will be analyzed using the multiple linear and Poisson regression or negative binomial regression, respectively. The mean difference and incidence rate ratio along with 95% confidence intervals will be reported for continuous and count outcomes respectively.

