All analyses will be adjusted for baseline values and sites. All statistical tests will be two-sided and all *p* values will be reported to three decimal places with those less than 0.001 reported as *p* < 0.001. The criterion for statistical significance will be set a priori at alpha = 0.05 and will be adjusted using the Bonferroni method for multiple testing for the co-primary outcomes. There will be no adjustment of alpha for secondary and subgroup analyses as these are exploratory. Analyses will be performed using R v3.6.1 [61].

We will perform sensitivity analyses of the primary outcomes to assess the effectiveness of Health TAPESTRY. We will adopt per-protocol approach to assess the effect of Health TAPESTRY at 6 months. In addition, we will assess the effect of Health TAPESTRY without adjusting for sites and baseline values. We will also use zero inflated Poisson or negative binomial distribution for the count data, depending on the distribution, to assess the robustness of the results.

Implementation: as noted above, implementation is assessed in three ways. For fidelity to the program, sites will be described as either high, medium, or low adherence to the program as intended. The qualitative data centered on implementation will be analyzed using a descriptive thematic analysis [62] and organized using NVivo 12 (QSR 2018) [63]. Transcripts will be independently coded inductively by two reviewers with qualitative analysis experience using open coding. A third reviewer will complete random code checking and provide oversight to ensure trustworthiness of the data. The interview questions will serve as the coding guide for the first few transcripts. The three reviewers will discuss and create a formal coding structure and review it regularly as more transcripts are coded to begin to collapse codes into over-arching themes. The themes will be aligned with the NPT constructs [26, 27].

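### Using one randomly chosen member per couple in the main analysis is unbiased, but it gives up precision that is partly recoverable and that the 586 makes no stated allowance for

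*Protocol article*

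**What the plan says.** All places are in the protocol article.

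- **Randomization and blinding:** where both members of a couple join, one is randomized and the other follows into the same group. In the main analysis one person's "data will be randomly selected for inclusion".
- **Procedures and data collection:** every participant in either group has volunteer visits at the start and at 6 months. Under Data collection, health care use is extracted from the electronic record. No exception is made for second partners.
- **Data analysis, Effectiveness:** "We will adopt intention-to-treat (ITT) as the primary analysis approach", with multiple imputation by chained equations. Physical activity gets a linear model and hospitalizations a Poisson or negative binomial model. Couples are not mentioned.
- **Data analysis, sensitivity analyses:** those listed are per-protocol, unadjusted and zero-inflated. None brings the second partner back.
- **Sample size:** 488 for physical activity ("corresponding to mean difference = 403 and SD = 1441"), "426 for number of hospitalizations", then "accounting for 20% lost to follow-up, we will require a sample size of 586 participants". No share of couples is given, and the text does not say whether the 586 is counted before or after one partner is set aside.

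**The concern.** The second partner has consented, been allocated, been visited twice and had a chart audit, and then contributes nothing to the main comparison. Couples are foreseeable, since recruitment approaches all rostered patients aged 70 or over and the protocol has a rule for them. Yet the sample size is stated in participants, while the main analysis counts at most one person per couple. If the 586 means people enrolled, the number analysed will be smaller than the calculation assumes. Physical activity sets the sample size, so it has no margin to absorb this. Part of the loss is avoidable with data the trial already collects.

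**Working it through.** **Inputs from the document.** Bonferroni level and power: "0.025 and power = 0.80" (Sample size). "All statistical tests will be two-sided" (Data analysis). Physical activity: difference 403, SD 1441. Hospitalizations: difference 0.14, SD 0.47. Loss to follow-up: 20%. Allocation: 1:1.

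**Assumptions (not in the document).** c is the share of participants who belong to an enrolled couple, taken as 5% to 40%. ρ is the within-couple correlation of the outcome, taken as 0.3 with other values shown.

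**1. Reproduce the plan's figures.** The number per arm is 2(z₀.₉₈₇₅ + z₀.₈₀)²(SD/δ)².

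- Physical activity: 2(2.2414 + 0.8416)²(1441/403)² = 243.05, so 244 per arm and 488 in total. This matches.
- Hospitalizations: 2(3.0830)²(0.47/0.14)² = 214.25, so 215 per arm and 430 in total, against 426 stated. This is close.
- Loss allowance: 488 × 1.2 = 585.6, so 586. This matches and leaves nothing over for couples.

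**2. Set the loss-allowance issue aside.** Dividing by 0.8 would give 610. With no couples at all, 586 × 0.8 = 469 completers and power is 0.784. That shortfall is separate from the couple rule, so the comparison below starts from the intended 488 completers.

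**3. Cost of the couple rule alone.** Dropping one partner leaves a fraction 1 − c/2. Power at total N is Φ[(δ/SD)√(N/4) − 2.2414]. For example, at c = 20%, N = 488 × 0.9 = 439.2, and Φ(0.2797 × 10.479 − 2.2414) = Φ(0.689) = 0.755.

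**4. Both partners kept, correlation modelled.** With efficient weighting, a couple carries the information of 2/(1 + ρ) people, so the effective fraction is (1 − c) + c/(1 + ρ). At c = 20% and ρ = 0.3 this is 0.80 + 0.20/1.3 = 0.954.

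| c | N, one dropped | Physical activity power, one dropped | Hospitalization power, one dropped | Effective N, both modelled (ρ = 0.3) | Physical activity power, both modelled |
|---|---|---|---|---|---|
| 0% | 488.0 | 0.802 | 0.853 | 488.0 | 0.802 |
| 5% | 475.8 | 0.791 | 0.843 | 482.4 | 0.797 |
| 10% | 463.6 | 0.779 | 0.833 | 476.7 | 0.792 |
| 20% | 439.2 | 0.755 | 0.811 | 465.5 | 0.781 |
| 40% | 390.4 | 0.699 | 0.759 | 443.0 | 0.759 |

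For physical activity the rule costs about 1, 2, 5 and 10 points of power. Modelling both partners recovers about 0.6, 1.2, 2.6 and 6 points at ρ = 0.3. At c = 20% the gain in effective sample is 9% for ρ = 0.1, 6% for 0.3 and 4% for 0.5.

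**5. Both partners kept, but in an unweighted regression with cluster-robust errors.** The variance is inflated by 1 + cρ, so the effective fraction is 1/(1 + cρ). This exceeds 1 − c/2 only if ρ < 1/(2 − c).

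- At c = 20% the limit is 1/1.8 = 0.56.
- At ρ = 0.3 the fraction is 1/1.06 = 0.943, against 0.900 for dropping one.
- At ρ = 0.7 it is 1/1.14 = 0.877, which is worse than 0.900.

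How the second partner is brought in therefore matters.

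**6. Enrolment if one partner is still dropped.** On the protocol's own basis this is 586/(1 − c/2): 602, 617, 652 or 733 for c = 5%, 10%, 20% or 40%.

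**The case against.** The rule is prespecified and valid. It yields independent observations and keeps the linear, count, zero-inflated and imputation models simple. Choosing a more efficient method over a valid one does not make the valid one an error. The share of couples is unknown, and at 5% the cost is about one point of power. Adjustment for baseline values may recover some power if the SD of 1441 is unadjusted, which is not stated. The article condenses a fuller protocol, and limiting the rule to the main analysis leaves room for both partners elsewhere. All of this stands and limits the size of the point. It does not remove it, because the rule and the sample size arithmetic are both fixed in the text shown.

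Three stronger readings are not supported.

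- **Breach of intention-to-treat.** A reader might infer that randomized people are being excluded. Only one partner is randomized, so the couple is in effect the randomized unit. Each couple is represented in its assigned arm by a pick that does not depend on outcome or adherence. A clarifying phrase beside the intention-to-treat statement is enough.
- **Power of 0.68 to 0.76 caused by couples.** Those values arise for shares of 40% down to 10% when starting from 586 with 20% loss. They mix in the separate loss-allowance shortfall, which gives 0.784 with no couples.
- **Keeping both partners always helps.** This holds under efficient weighting for any correlation below 1. It fails for unweighted regression with cluster-robust errors when the correlation is high (step 5).

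**Conclusion.** The point holds as a matter of efficiency and sample size accounting, not of bias. The main analysis leaves out one followed member of each couple, and the stated 586 makes no allowance for it. The cost to physical-activity power runs from about 1 point at a 5% couple share to about 10 at 40%. Slightly more than half of that is recoverable at a correlation of 0.3. Hospitalization power, on the plan's own inputs, stays above 0.80 up to a 20% share and falls to 0.76 at 40%. The direction is certain if the 586 counts people enrolled. If it counts independent units, the accounting part falls away and only the unused data remain. The size rests on the assumed couple share and correlation and on a comparison of means without baseline adjustment.

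**What to change.** - In the main analysis include both partners and model the within-couple correlation in the linear and the count models. Use GEE with an exchangeable working correlation or a couple random effect, with robust errors and single participants as clusters of one. Do not rely on unweighted regression with cluster-robust errors alone.
- Keep one-per-couple as a sensitivity analysis.
- Make the imputation respect the pairing, for example by using the partner's data.
- Under Sample size, state whether "we will require a sample size of 586 participants" refers to people or to independent units, and give the couple share assumed. If one partner will still be dropped, raise enrolment as in step 6.
- Beside the intention-to-treat statement, say how couples enter the analysis set.

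The cost is protocol or analysis-plan wording and somewhat more complex models and imputation. The analysis change needs no new data.
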